### **3.2.2.3 INCT compared to CNCT**

This will be the first study to perform a prospective comparison between patients treated with INCT and CNCT. INCT addresses occult micrometastasis earlier but delays the delivery of CRT, defying the principle that the interval from the start of treatment to the end of radiation should be as short as possible. On the other hand, CNCT delays treatment of micrometastasis for several weeks compared to INCT but does not delay CRT, and may increase tumor response by reducing the time from initiation of therapy to completion of radiation. By assessing tumor response and other measurable outcomes during and after treatment, we may be able to compare INCT and CNCT in terms of organ preservation,

treatment compliance and adverse events. We will also be able to determine the impact of each component of TNT on tumor response.

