## **4.0 OVERVIEW OF STUDY DESIGN/INTERVENTION**

## 4.1 Design

This is a multicenter phase II study investigating the efficacy of TNT and selective NOM in patients with LARC. Patients with MRI-staged Stage II (uT3-4, uN-) or Stage III (any T, N+) rectal cancer and would be considered to require a complete TME at baseline will be randomized to receive FOLFOX/CapeOX before (Arm 1 or INCT) or after (Arm 2 or CNCT) 5-FU or capecitabine-based CRT. An interval evaluation will be conducted after completion of INCT in Arm 1, and after completion of CRT in Arm 2. Patients with tumors progression at the time of the interval evaluation will be treated according to standard practice per treating institution guidelines. Those with evidence of stable disease or tumor response will complete neoadjuvant therapy. Patients in both arms will be re-staged after completion of all neoadjuvant therapy. Patients with incomplete response will undergo a TME. Patients with complete or near complete clinical response will be treated with NOM. Criteria for determining complete, near complete and no incompleteresponse are outlined in Section 9.3.2. Patients in both groups (TME and NOM) will be followed according to NCCN guidelines. For study purposes, all patients will be followed for five years from the last date of treatment. For patients in the TME group, last date of treatment will be the date of surgery. For NOM patients, including those who undergo subsequent TME, last date of treatment is the last date of neoadjuvant treatment. Patients in the NOM group will be evaluated using rectal MRI and endoscopic exam (see section 10). Patients in the NOM group who undergo subsequent TME will be followed according to current NCCN guidelines. All patients will be followed based on intent-to-treat. Disease-free survival will be measured after three years.

The study is designed to test the hypothesis that patients with LARC treated with TNT and TME or NOM will have an improved 3-year DFS compared to patients with similar tumors treated with CRT, TME and ACT. We will measure QoL in patients treated with TNT and TME with patients treated with TNT alone. We will also compare INCT to CNCT with respect to organ preservation at 3 years, compliance with treatment, adverse events, and surgical complications.

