## 4.2 Intervention

The neoadjuvant chemotherapy regimen is prescribed specifically as 8 cycles of FOLFOX or 5 cycles of CapeOX over a period of approximately 15-16 weeks. The CRT regimen consists of the standard algorithms: a total of 5400-5600 cGy of radiation (4500 cGy to the pelvis, with an integrated boost to the primary tumor and involved nodes of 500 cGy, followed by an optional 400-600 cGy boost to the primary tumor and involved nodes) delivered in 27-28 fractions, respectively, of 180-200 cGy each over a 5-6 week period. Starting on the first day of RT, patients receive 5-FU administered by continuous infusion or capecitabine for the duration of the radiotherapy.

An interval evaluation will be conducted after completion of INCT in Arm 1, and after completion of CRT in Arm 2. Patients with tumor progression at interval evaluation will be treated according to standard practice as per treating institution guidelines; those with evidence of response or stable disease will complete neoadjuvant therapy. Patients in both arms will be re-staged after completion of all neoadjuvant therapy. Those with a clinical response insufficient to warrant non-operative management safely at the time of re-staging evaluation will undergo a TME. Patients with near complete clinical response or clinical complete response will be treated with NOM. Patients in both arms (TME and NOM) will be followed according to NCCN guidelines. Patients in the NOM group will be evaluated using rectal MRIs and endoscopic exam (see section 10). Patients in the NOM group who undergo subsequent TME will be followed according to current NCCN guidelines.

Pathology assessment of the surgical specimens will be performed according to the College of American Pathologists guidelines. Completeness of the mesorectal excision, tumor regression grade (TRG), and tumor staging will be categorized according to the criteria specified in the current edition of the AJCC Staging Manual.[87]

Safety will be assessed by documenting adverse events during TNT and after surgery. Adverse events will be graded according to NCI CTCAE version 4.0, and surgical complications will be graded according to the Clavien-Dindo classification.[88] Refer to Appendix N to see the classification scale.

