## 9.0 TREATMENT/INTERVENTION PLAN

### 9.1 Neoadjuvant Chemotherapy

There are several variations of the basic FOLFOX regimen. The specific version of the FOLFOX regimen that will be used in this trial is modified, or mFOLFOX6. This entails administration of 5-FU and leucovorin all on day 1 (in contrast to the FOLFOX4 regimen, where this is divided over 2 days) and administration of 85 mg/m^2 of oxaliplatin. Instead of referring to the regimen as mFOLFOX6, we refer to this neoadjuvant regimen, more simply, as FOLFOX.

Patients will receive 8 cycles of FOLFOX, administered every other week. FOLFOX will be given on Day 1 of each cycle. Patients will receive oxaliplatin 85 mg/m^2 IV (over 120 minutes or according to standard institutional guidelines), leucovorin 400 mg/m^2 IV (over 120 minutes or according to standard institutional guidelines), 5-FU 400 mg/m^2 IVP, and 5-FU 1200 mg/m^2/day CIV over 2 days (total dose of 2400 mg/m^2 over 46-48 hours) for a total of 16 weeks/8 cycles.

For patients receiving CapeOX; Oxaliplatin will be delivered at 130 mg/m^2 over two hours day 1 or according to standard institutional guidelines, and capecitabine at 1000mg/m^2 BID days 1-14. They will be repeated on a 21 day cycle, for a total of 15 weeks/5 cycles (maximum total cumulative oxaliplatin dose 650 mg/m^2). To track compliance, patients will be asked to complete a pill diary for each cycle of CapeOX (Appendix G).

In an effort to prevent adverse events, all patients will be treated with anti-emetics and supportive agents as per institutional guidelines. For patients treated outside of MSKCC, supportive and antiemetic agents may be administered per that institution's standard

practices. If the institution does not have a standard practice, then these may be administered at the discretion of the primary oncologist.

The FOLFOX and chemoradiotherapy regimens used in this clinical trial represent the standard care for treatment of patients with locally advanced rectal cancer. Therefore, all clinicians recruiting study subjects have considerable experience with this regimen. The toxicity of each specific agent is outlined below. The regimens used in this clinical trial also represent standard care for patients with locally advanced rectal cancer.

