Based on previous data, we anticipate a 20% NOM in the INCT arm, and 35% in the CNCT arm, after 3 years. The proportion of patients initially entered in the NOM protocol will be higher, but some will later relapse and require TME. For this reason, we anticipate that the proportion of patients with NOM at 3 years will be close to the pCR rates observed in previous studies. We estimated that the 222 patients required for the primary aim would be sufficient to detect differences in organ preservation rates. Our preliminary results indicate that the proportions of patients selected for NOM based on tumor response after completion of neoadjuvant therapy are much greater than expected: 66% in one arm and 79% in the other. Although many of these patients may eventually experience tumor regrowth requiring total mesorectal excision, the proportions of patients with a preserved rectum 3 years after diagnosis are likely to be greater than the original estimates. Therefore, based on the new information, we plan to increase accrual to 325 patients. There is limited information regarding treatment compliance and adverse events in patients who have received more than 4 or 6 cycles of INCT or CTNT. Therefore, these secondary objectives are considered exploratory. If both arms meet the endpoint in primary objective, we plan to use NOM rate to determine the more promising regimen using a “pick the winner” strategy. We will calculate the number of patients treated with NOM who are alive and free of disease 3 years following the start of the study. We will require at least 20 NOM patients in each arm to employ the following strategy: If there is a difference of 5 NOM patients between arms, the arm with more NOM patients will be deemed the winner. With 101 patients in each arm, 20% NOM in patients treated with INCT and 30% in patients treated with CNCT, we will have an 83% probability of selecting CNCT, a 1% probability of selecting INCT, and a 16% probability of considering the study inconclusive.

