The measurement will be the presence of tumor specific mutations—defined as mutations present in the pretreatment biopsy—in plasma DNA of patients in both study groups at different time points (see Section 10.0). A second measurement for this aim will be the plasma miRNA profiles at the same time points as above. We will graphically examine these two measurements in patients treated successfully with NOM plus patients with ypT0 after TME and with patients who had residual tumor after TME.

As this will be the first prospective study investigating the circulating tumor DNA and miRNA profiles in rectal cancer patients treated with TNT and NOM, this aim will be considered exploratory.

Patients who take part in this portion of the study will be from Memorial Sloan Kettering only. Given the smaller sample size, all analyses will be descriptive. We will graph each measurement over time for the two groups defined above. If possible, comparisons at each time point will be done using nonparametric methods, such as the Wilcoxon rank-sum test.

*14.4.3 Use of genomic analysis by next generation sequencing to profile rectal cancer treated with neoadjuvant chemotherapy and radiation.*

The measurements for this study will be the mutation profile, copy number alteration profile, and gene expression profile in pretreatment tumor biopsies of patients treated in both study arms. We will compare the results in patients treated successfully with NOM plus patients with ypT0 after TME, with patients who had residual tumor after TME.

As this will be the first prospective study investigating the genomic profile of rectal cancer patients treated with TNT and NOM, this aim will be considered exploratory.

*14.4.4 Investigation of the molecular mechanisms of tumor resistance to neoadjuvant therapy by genomic analysis of rectal cancer before and after treatment.*

The endpoint for this study will be the proportion of cells expressing the colonic stem cell biomarkers in pretreatment tumor biopsies of patients treated in both groups. We will compare the results in patients treated successfully with NOM plus patients with ypT0 after TME and compare them with patients who had residual tumor after TME. In addition we will investigate the expression of colonic stem cell biomarkers in the surgical specimens of patients with residual tumor after TME.

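### The ctDNA/miRNA comparison in 14.4.2 has no arm term, yet the interval sample follows chemotherapy at about week 19-20 in Arm 1 and chemoradiation at about week 9-10 in Arm 2

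*Protocol*

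**What the plan says.** Section 14.4.2 measures tumor-specific mutations in plasma DNA, and plasma miRNA profiles, at the Section 10.0 time points. It contrasts patients managed successfully by NOM plus those with ypT0 after TME with patients who had residual tumor after TME. On the analysis it states "We will graph each measurement over time for the two groups defined above" and then "If possible, comparisons at each time point will be done using nonparametric methods, such as the Wilcoxon rank-sum test". The aim covers both protocol arms, is restricted to MSKCC patients, and is called exploratory and descriptive.

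The Section 10.0 schedules mark research blood at baseline, interval evaluation and re-staging in both arms. Footnote 7 makes the on-treatment draw optional and ties it to routine labs. Section 4.1 fixes what the interval visit follows: "An interval evaluation will be conducted after completion of INCT in Arm 1, and after completion of CRT in Arm 2".

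Section 14.2 anticipates 3-year NOM of 20% in the INCT arm and 35% in the CNCT arm. It reports preliminary selection for NOM of "66% in one arm and 79% in the other", without saying which arm is which.

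**The concern.** The two groups are defined by outcome across both arms, and no stratification or display by arm is given. Followed as written, the interval point on each curve mixes two kinds of sample: chemotherapy without radiation, and chemoradiation without FOLFOX/CapeOX, about ten weeks apart from the start of treatment.

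If the marker level at that visit depends on which component has been given or on elapsed time, and if the arms contribute differently to the two outcome groups, a difference between the curves can reflect arm rather than response. The aim is to see whether these markers can monitor response to TNT, and the interval draw is the scheduled on-treatment sample.

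**Working it through.** **Inputs.** FOLFOX runs "for a total of 16 weeks/8 cycles" and CapeOX "for a total of 15 weeks/5 cycles" (9.1). Radiation is "delivered in 27-28 fractions, respectively, of 180-200 cGy each over a 5-6 week period" (4.2). The interval visit is 4 weeks ± 2 after the last chemotherapy (Arm 1) or the last radiation (Arm 2), and the gap between components is at most 8 weeks (9.3.1). Re-staging is 8 weeks ± 4 after the end of TNT (9.3.2). The correlative cohort is 80 patients, about 40 per arm (14.4).

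**Reproducing a stated figure.** Section 3.5 puts re-staging at about 30-40 weeks from the start of TNT. Chemotherapy 15-16 + gap 4-8 + CRT 5-6 + 8 = 32-38 weeks, or 28-42 with the ± 4 week window. The durations agree with the protocol's own figure.

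**Interval sample**, if drawn at the interval visit.
- Arm 1: 15-16 + 4 = week 19-20; window 15 + 2 to 16 + 6 = 17-22.
- Arm 2: 5-6 + 4 = week 9-10; window 5 + 2 to 6 + 6 = 7-12.

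The windows do not overlap. Even if the visit fell immediately after treatment ended, Arm 1 would be at week 15 or later and Arm 2 at week 12 or earlier.

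**Re-staging sample.** Total elapsed time is similar in the two arms. Time since radiation is 8 weeks in Arm 1 (4-12) and 4 + 15-16 + 8 = 27-28 weeks in Arm 2 (2 + 15 + 4 = 21 to 8 + 16 + 12 = 36).

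**Is arm tied to outcome group?** NOM rates serve as a proxy for the groups; this ignores ypT0 after TME. With 40 per arm:
- 20%/35%: NOM 8 and 14, so Arm 1 is 8/22 = 36% of the NOM group and 32/58 = 55% of the TME group.
- 66%/79%, assigned to Arms 1 and 2 by assumption: 26.4/58 = 46% and 13.6/22 = 62%.
- 20%/30%, the rates in the selection rule of 14.2: 8/20 = 40% and 32/60 = 53%.

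**What that could do.** The protocol gives no marker values, so any arm difference is an assumption. A simulation used 40 patients per arm, a normally distributed marker, no response effect within arm, and an assumed arm shift at the interval sample. The unstratified rank-sum test at nominal 5% rejected as follows:

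| NOM rates | no shift | 0.5 SD | 1 SD | 2 SD |
|---|---|---|---|---|
| 20%/35% | 4.6% | 5.9% | 10.7% | 19.6% |
| 66%/79% | 5.3% | 5.4% | 8.6% | 15.8% |
| 20%/30% | 4.9% | 5.5% | 7.9% | 11.7% |

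On the detection scale, assume 60% in Arm 1 and 20% in Arm 2, unrelated to response, with the 20%/35% rates. The NOM group shows (8 × 0.6 + 14 × 0.2)/22 = 34.5% and the TME group (32 × 0.6 + 26 × 0.2)/58 = 42.1%, a spurious gap of 7.5 points. Swapping the detection rates reverses its sign.

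**Cost of stratifying.** With an assumed true response effect of 0.8 SD, a van Elteren test had 81-84% power for arm shifts of 0, 1 and 2 SD. With no shift, the unstratified test had 83-86%, so stratifying cost about 1-2 points.

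**The case against.** The best reply is that pooling is implied, not stated. Section 14.4.2 never says arm will be ignored, the Section 10.0 schedules are set out by arm, the test is only an example to be used where possible, and stratification could sit in a statistical analysis plan. That stands as a limit on how firmly the point can be put. It does not remove it: the protocol itself chose the groups, the display and an example test, and arm enters none of them. For QoL, by contrast, Section 14.3 says that differences by treatment will be examined.

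It is also true that the aim is exploratory, single-centre and descriptive, that no decision depends on it, and that the affected draw is optional. The possible bias may be small. In the 60%/20% illustration, the standard error of the difference is √(0.345 × 0.655/22 + 0.421 × 0.579/58) ≈ 12 points, so the 7.5-point gap is about 0.6 of a standard error.

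Three stronger readings are tempting and not supported.
- A reader might infer that the plan defeats a purpose set out in 3.2.2.3. That section says "We will also be able to determine the impact of each component of TNT on tumor response"; it concerns tumor response, not ctDNA or miRNA. Arm is known for every randomised patient, so nothing prevents a later display by arm.
- A reader might extend the point to interval MRI. Section 14.4.1 specifies its change measures only between baseline and post-TNT, so no such interval comparison is planned there.
- A reader might infer that every time point is compromised. Baseline precedes treatment in both arms, and re-staging follows the whole of TNT at a similar total time.

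**Conclusion.** The point holds at minor priority. At the interval sample, an outcome-group comparison without arm sets together samples that differ in treatment received and by about ten weeks in timing, and the protocol's own NOM rates tie arm to outcome group. That is enough for confounding if the marker differs between arms at that visit.

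The timing follows from the protocol's durations, given that the optional tube is drawn at the interval visit. The consequence rests on assumptions: NOM rates as a proxy for the outcome groups, and an arm shift for which the protocol has no data. Under those assumptions, false-positive rates run from close to nominal at 0.5 SD to about 12-20% at 2 SD. Re-staging is a lesser concern (about 8 against 27-28 weeks since radiation), baseline is unaffected, and the primary objective is not touched.

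**What to change.** In 14.4.2, label the interval sample as taken after INCT (Arm 1) or after CRT (Arm 2). Graph the two outcome groups within each randomised arm. Stratify any rank-sum comparison at the interval and re-staging samples by arm, for example with the van Elteren test.

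This is a change of wording and needs no extra samples. The price is fewer patients behind each curve; the stratified test still combines the information from both arms.

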## **14.5 Stopping rules**

To ensure patient safety, we have introduced a stopping rule for R1 resections among NOM patients requiring TME. The rate of R1 resection after TME in similar patient populations ranges from 5% to 10%. For our trial, we consider an R1 resection rate of 10% acceptable, and 25% unacceptable. Continuous monitoring based on repeated significance testing will be implemented.[96] We will stop the trial if the number of R1 resections in the NOM group requiring TME exceeds the numbers listed below. Based on these rules, the probability of crossing the boundary is 10% if the true toxicity rate is 10% and is 99% if the true toxicity rate is 25%.

|                                 |   |   |    |    |    |    |    |    |    |    |    |    |    |
|---------------------------------|---|---|----|----|----|----|----|----|----|----|----|----|----|
| Patients in NOM who require TME | 2 | 6 | 11 | 17 | 23 | 29 | 36 | 43 | 50 | 57 | 64 | 71 | 79 |
| R1 Resection (positive margins) | 1 | 2 | 3  | 4  | 5  | 6  | 7  | 8  | 9  | 10 | 11 | 12 | 13 |

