In addition, we will calculate therapy compliance using the following measures: the number of days RT was held, the number of RT delays of  $\geq 1$  week, the number of dose delays and the number of dose reductions in INCT and CNCT. We will also calculate the rate of select hematologic events (as outlined in 17.2), select non-hematologic events (as outlined in 16.0), and unexpected Grade 3 or higher non-hematologic adverse events and surgical complications in each treatment arm. Comparisons will be done using the Wilcoxon Rank Sum test or the Fisher’s Exact test.

**14.3 Secondary objective 2.:** *To measure patient-reported functional outcomes and QoL in patients with LARC treated with NCT, CRT and NOM, and compare these to patients treated with TME.*

The primary analyses for this aim will use data combined across both treatment arms; however, differences according to treatment will also be investigated. The primary endpoint will be QoL as measured one year from the end of TNT. Secondary endpoints will be bowel, sexual, and bladder function. While the subscales will be reported, the primary secondary endpoints will be the total scores on the BFI, FSFI and IIEF. With a total of 325 patients accrued, we expect that 129 patients will obtain complete clinical response and 196 will undergo TME. Approximately 15 to 30 patients initially treated with NOM are expected to cross over to TME at some point during follow-up. For the primary analyses, the NOM group will include these cross-overs on an intent-to-treat analysis. In secondary analysis, patients who eventually crossed over to receive surgery will be included in the TME group. We define this analysis as a comparison between TME vs. durable NOM. Durable NOM is defined as 3-year disease-free survival. We expect that 70% of patients will complete the QoL assessment at 1 year. This response rate takes into account refusals to complete the QoL

questionnaires, and the approximately 20% of patients who will develop distant disease or die before the 1-year time point. Thus, at 1 year we expect to have information on 94 TME patients and 62 NOM patients.

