## 16.2 Data and Safety Monitoring

The Data and Safety Monitoring Plan utilized for this study must align with the MSK DSM Plan where applicable.

The Data and Safety Monitoring (DSM) Plans at Memorial Sloan Kettering were approved by the National Cancer Institute in August 2018. The plans address the new policies set forth by the NCI in the document entitled "Policy of the National Cancer Institute for Data and Safety Monitoring of Clinical Trials."

There are several different mechanisms by which clinical studies are monitored for data safety and quality. At a departmental/PI level, there exist procedures for quality control by the research team(s). Institutional processes in place for quality assurance include protocol monitoring, compliance and data verification audits, staff education on clinical research QA, and two institutional committees that

are responsible for monitoring the activities of our clinical trials programs. The committees: Data and Safety Monitoring Committee (DSMC) for Phase I and II clinical trials, and the Data and Safety Monitoring Board (DSMB) for Phase III clinical trials, report to the Deputy Physician-in-Chief of Clinical Research.

The degree of monitoring required will be determined based on level of risk and documented.

The MSK DSMB monitors phase III trials and the DSMC monitors non-phase III trials. The DSMB/C have oversight over the following trials:

- MSK Investigator-Initiated Trials (IITs; MSK as sponsor)
- External studies where MSK is the data coordinating center
- Low risk studies identified as requiring DSMB/C review

The DSMC will initiate review following the enrollment of the first participant, or by the end of the year one if no accruals, and will continue for the study lifecycle until there are no participants under active therapy and the protocol has closed to accrual. The DSMB will initiate review once the protocol is open to accrual.

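### The R1 stopping rule's stated 99% chance of catching a 25% R1 rate carries no patient number, and it is not delivered at the 15 to 30 TMEs among NOM patients that the protocol expects

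*Protocol*

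**What the plan says.** Section 14.5 sets one stopping rule, for R1 resections among NOM patients who go on to TME. Its premise is that "we consider an R1 resection rate of 10% acceptable, and 25% unacceptable". On method, "Continuous monitoring based on repeated significance testing will be implemented", and the action is stated as "We will stop the trial if the number of R1 resections in the NOM group requiring TME exceeds the numbers listed below". The boundary is a two-row table. The patient row begins "Patients in NOM who require TME | 2 | 6 | 11 | 17 | 23 | 29 | 36 | 43 | 50" and runs on to 79. The R1 row begins "R1 Resection (positive margins) | 1 | 2 | 3 | 4 | 5 | 6 | 7 | 8 | 9" and runs on to 13. The section then claims that "the probability of crossing the boundary is 10% if the true toxicity rate is 10% and is 99" per cent if the true rate is 25%. It names no number of patients for these two probabilities.

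Section 14.3, written for 325 patients with 129 in the NOM group, forecasts the population that the rule counts: "Approximately 15 to 30 patients initially treated with NOM are expected to cross over to TME at some point during follow-up".

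Section 14.2 reports that 66% of one arm and 79% of the other were selected for NOM, and says that many of these patients may later need TME.

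Section 16.2 says that review by the Data and Safety Monitoring Committee (DSMC) "will continue for the study lifecycle until there are no participants under active therapy and the protocol has closed to accrual".

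**The concern.** The chance that a sequential boundary is crossed grows with the number of patients observed, so 10% and 99% mean nothing without that number. The rule can count only NOM patients who have TME, and the protocol's one explicit forecast of them is far below the 79 at which its table ends.

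This is the only rule in Section 14.5, and it guards against a risk named in Section 17.0: relapse during NOM that surgery cannot salvage. An ethics board or monitoring committee reading Section 14.5 would take a 25% R1 rate as almost certain to be caught. If the detection probability is much lower, the absence of a boundary crossing would be wrongly read as reassurance.

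**Working it through.** **Inputs.** From Section 14.5: acceptable rate 0.10; unacceptable rate 0.25; patient numbers 2, 6, 11, 17, 23, 29, 36, 43, 50, 57, 64, 71, 79; R1 counts 1 to 13; continuous monitoring; stop when the count exceeds the listed number. From Section 14.3: 15 to 30 crossovers, 129 NOM patients, 325 accrued. From Section 14.2: 66% and 79% selected for NOM.

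**Method.** Let X(n) be the R1 count after n TMEs and c(n) the count listed in the first column whose patient number is at least n. The trial stops the first time X(n) > c(n). Write f(n, x) for the probability of having x R1 resections after n TMEs without having stopped. Then f(n, x) = (1 − p)·f(n − 1, x) + p·f(n − 1, x − 1). After each patient, all mass with x > c(n) is removed and added to the crossing probability. As a check by hand, at n = 2 the rule stops only on two R1 resections: 0.25² = 0.0625 and 0.10² = 0.010.

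**The plan's own figure.** At 79 TMEs the result is 9.1% (true rate 10%) and 97.0% (true rate 25%). The first agrees with the stated 10% after rounding. The second is about two points short of 99%. If the boundary is continued past 79 in steps of 7 to 8 patients per additional R1 (an assumption), 101 TMEs give 9.9% and 99.0%. Both stated figures therefore fit a maximum of about 100.

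**At other numbers of TMEs, same rule:**

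| TMEs in NOM patients | Crossing, true rate 10% | Crossing, true rate 25% |
|---|---|---|
| 15 | 3.7% | 40.1% |
| 20 | 4.5% | 51.2% |
| 30 | 5.8% | 68.6% |
| 45 | 7.1% | 83.8% |
| 60 | 8.1% | 91.9% |
| 79 | 9.1% | 97.0% |

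Detection first reaches 80% at 41 TMEs and 90% at 56.

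**Other readings of the rule:**
- Checked only at the listed columns: detection is 33% at 15 and 69% at 30.
- Stopping when the count reaches, rather than exceeds, the listed number: 99.0% at 79, but false stopping is then 33%. At 15 to 30 TMEs, detection is 73% to 88% with false stopping of 26% to 30%.
- The previous column's limit carried forward: 64% to 83% at 15 to 30, but false stopping is 13% to 16% there and 21% by 79.

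None of these gives both 10% and 99% within the printed table.

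**Sensitivity to the newer NOM rates.** 66% of 325 is about 214 and 79% is about 257. The crossover fraction implied by Section 14.3 is 15/129 = 11.6% to 30/129 = 23.3%. If it applies unchanged (an assumption), the lowest case is 0.116 × 214 ≈ 25 TMEs and the highest 0.233 × 257 ≈ 60. Detection is then 60.6% to 91.9%. With equal arms, NOM selection averages 72.5%, about 236 patients, giving 27 to 55 TMEs and 64% to 90%.

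**The case against.** The best defence is that the 15 to 30 comes from a quality-of-life sample-size paragraph resting on 129 NOM patients, while Section 14.2 has newer data pointing to about 236. If 20%, 30% or 40% of 236 had TME (assumptions), that would be 47, 71 or 94 patients. Detection would be 85%, 95% or 99%, the last on the extended boundary. A table running to 79 is then not unreasonable. This stands in part: 40% to 69% follows from Section 14.3 and is not the only figure that the protocol supports. It does not rescue the single 99%, because Section 14.3 is current text for the 325-patient trial and the two sections imply different numbers.

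Three stronger readings are tempting, and the documents do not support them:

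- **That the 10% and 99% are a calculation error, or belong to 79 patients.** Section 14.5 ties them to no number, and a maximum near 100 reproduces both. The fault shown is an unstated number out of line with the forecast.
- **That monitoring of the boundary will lapse before most resections occur.** Section 14.5 does not assign the boundary to the DSMC, and Section 16.2 also describes quality control at departmental and investigator level. Nothing gives the timing of regrowth surgery in this trial, and staggered accrual means that some of it can fall while accrual is open. What remains is a gap: NOM follow-up runs to 60 months, the text leaves open whether surveillance counts as active therapy, and nobody is named to watch the boundary once DSMC review ends.
- **That the boundary must be recomputed to use its full 10% allowance.** False stopping of 3.7% to 5.8% is within the stated 10%. Changing a safety boundary after preliminary results are known has its own drawbacks.

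**Conclusion.** The concern holds. The stated 99% has no patient number attached, is not reached within the printed table under the rule as worded, and is well above what the rule delivers at the protocol's own forecast. At 15 to 30 TMEs, a true R1 rate of 25% would go undetected with probability 60% to 31%. With the higher NOM selection rates and an unchanged crossover fraction, it would go undetected with probability about 39% to 8%.

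These figures assume the literal rule, a check after every TME, independent outcomes and a constant R1 rate. The figure of about 100 TMEs also assumes that the boundary continues at the same spacing, and the 25 to 60 range assumes that the crossover fraction carries over to a larger NOM group. A higher crossover fraction would bring detection closer to 99%. This is a material overstatement of a safety property. It is not evidence that the boundary itself is unsound.

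**What to change.** In Section 14.5, state the number of NOM patients having TME that 10% and 99% assume. Replace the single pair with crossing probabilities at both rates over the plausible range, for example 15, 30, 45, 60 and 79. Say whether the boundary is checked after every patient or only at the listed columns.

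Reconcile the expected number of NOM patients needing TME across Sections 14.2, 14.3 and 14.5, so that the quality-of-life forecast and the stopping rule rest on the same NOM group.

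In Section 14.5 or 16.2, say that this boundary is monitored until NOM follow-up ends, and by whom.

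The cost is one exact calculation, a short table and a few sentences, with no change to the boundary or to data collection. The stated detection probability will look less favourable. Recomputing the boundary for a smaller number of TMEs is optional. If it is considered, the reasons should be recorded, because preliminary results are already known.
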